## Abstract

**Background:**

HPV-related anal cancer occurs in excess rates among people living with HIV (PLWH) and has been increasing in incidence. The HPV vaccine is an effective and safe approach to prevent and reduce the risk of HPV-related disease. Yet, HPV vaccine programs tailored and implemented in the HIV population are lagging for this high-risk group.

**Methods:**

A pre-post intervention study design will be used to tailor, refine, and implement the 4 Pillars™ Practice Transformation Program to increase HPV vaccination among PLWH. Guided by the RE-AIM framework, the CHAMPS study will provide training and motivation to HIV providers and clinic staff to recommend and administer the HPV vaccination within three HIV clinics in Georgia. We plan to enroll 365 HIV participants to receive HPV education, resources, and reminders for HPV vaccination. Sociodemographic, HPV knowledge, and vaccine hesitancy will be assessed as mediators and moderators for HPV vaccination. The primary outcome will be measured as an increase in uptake rate in initiation of the HPV vaccine and vaccine completion (secondary outcome) compared to historical baseline vaccination rate (control).

**Discussion:**

The proposed study is a novel approach to address a serious and preventable public health problem by using an efficacious, evidence-based intervention on a new target population. The findings are anticipated to have a significant impact in the field of improving cancer outcomes in a high-risk and aging HIV population.

**Trial registration:**

NCT05065840; October 4, 2021.

## Background

HPV-related anal cancer occurs in excess rates among people living with HIV (PLWH) [1], and has been increasing in incidence [1]. Notably, the incidence of anal cancer among men who have sex with men (MSM) is 20- to 40- fold greater relative to non-MSMs [2]. The Human Papillomavirus (HPV) is responsible for 90% of anal cancers where oncogenic HPV type 16 is responsible for 90% of anal cancers [3]. It is presumed the increased risk for anal cancer among PLWH is due to an impaired ability to clear HPV infections and increased reactivation of latent HPV infection. Of note, highly active antiretroviral therapy (HAART) has modest to no effect on HPV clearance or persistence; thus, other mechanisms may be involved that result in cellular immune dysfunction [4].

The safety and efficacy of the HPV vaccine has been evaluated in PLWH and is shown to be safe and highly immunogenic against oncogenic HPV types 16 and 18 [5–8]. The HPV vaccine also has been shown to decrease the risk of HPV-related anal intraepithelial neoplasia in a sample of MSMs [9]. Thus, anal cancer can be potentially a preventable disease through the use of the HPV vaccine [3]. However, very limited research has been conducted on the uptake of HPV vaccination among PLWH. One study found among a sample of young MSM’s who self-reported as HIV-positive, HPV vaccine initiation was 13.4% [10]. Although uptake is low, studies of the acceptability of the HPV vaccine has been found to be high among high risk groups like MSMs [11–13].

The United States’ Advisory Committee on Immunization Practices (ACIP) recommends vaccination up to age 26 years and recently FDA (Food and Drug Association) approved up to age 45 years for women and men [14]. ACIP also advises individuals who are immunocompromised to receive the 3-dose series of the HPV vaccine up to age 26 years of age and with shared clinical decision making for those 26 years and older. The Center for Disease Control and Prevention (CDC) urges catchup vaccination for adults who have not been previously vaccinated and remain vulnerable to develop preventable HPV-related cancers [15]. Yet, there is a dearth of studies that have tailored and implemented evidence-based approaches to promote HPV vaccination among PLWH and eligible for catchup vaccination. Since intervention development is costly, complex, and time consuming, we seek to refine and tailor an existing, evidence-based intervention and integrate in a new population and new setting. The CDC’s 4 Pillars™ Practice Transformation Program (4 Pillars™ Program) is a robust and empirically supported strategic approach that promotes the uptake of adult vaccinations and addresses facilitators and barriers at the patient, provider, and clinic level [16]. The 4 Pillars™ Program incorporates these recommendations via “a menu” of strategies to promote the establishment and maintenance of vaccination into routine practice (Table 1).

**Table 1 Tab1:** The 4 Pillars Practice Transformation Program^TM^: Evidence-based strategies to increase vaccination

Pillar 1: Convenient and easy accessibility	• Use every patient visit type as an opportunity to vaccinate. • Offer open access/walk-in vaccination during office hours. • Promote simultaneous vaccination. • Hold express vaccination clinics outside normal office hours where only influenza or other adolescent vaccines are offered and systems for check-in, screening, and record-keeping are streamlined. • Create a dedicated vaccination station.
Pillar 2: Patient communication/education	• Provide information about vaccine preventable diseases at the beginning of every visit. • Enroll patients in electronic health portal. • Train staff to discuss vaccines during routine processes. • Discuss the serious nature of vaccine preventable diseases. • Use clinic messages, poster, fliers, electronic message board, website posting, and social media to promote vaccination. • Reach out by email, phone, text, mail, health portal to recommend vaccines that are due.
Pillar 3: Enhanced systems to promote vaccination	• Ensure sufficient vaccine inventory. • Assess vaccination eligibility for every patient encounter. • Assess immunizations as part of vital signs. • Review and update accurate EMR vaccination record keeping. • Establish standing order protocols.
Pillar 4: Motivation	• Create a chart to track progress. Set an improvement goal and regularly track progress. • Provide ongoing feedback to staff on vaccination progress. • Create a competitive challenge/provide reward for successful results among staff.

The 4 Pillars™ Program has shown to improve vaccination rates among high risk adults in primary care practices that successfully implemented strategies across the program [17, 18]. A randomized controlled cluster trial (RCCT) found the 4 Pillars Program significantly increased HPV vaccination among a cohort of 10,861 adolescent patients in primary care practices [19]. The intervention sites increased baseline HPV vaccination by 10.2 percentage points (PP) versus 7.3 PP in the control sites (*p* < .001) [19]. Furthermore, another large RCCT of adolescents found the 4 Pillars™ Program significantly increased baseline initiation of HPV vaccination by 17.1 PP (*p* < .001) and increased HPV completion by 14.8 PP (*p* < .001) [20]. These findings highlight the effectiveness of the 4 Pillars™ Program to increase HPV vaccination in the general population.

The Advancing HPV vaccination for HIV Positive Adults (CHAMPS) study seeks to expand the success of the 4 Pillars™ Program and tailor, refine, and implement in the HIV positive population, who are at high risk for HPV-related cancers and can obtain the most benefit from the vaccine. The strategies selected from the 4 Pillars™ Program are based on an extensive review of the HIV and related literature (Table 2) [21–28]. The intervention will be implemented in three HIV community clinics in Georgia, USA and enroll *n* = 365 PLWH, age 18–45 years, from those clinics. Guided by the RE-AIM framework, the proposed specific aims are:Tailor and refine the 4 Pillars™ program for implementation in three HIV community clinics in Georgia.Test the effectiveness of the 4 Pillars™ program as measured by an increase in uptake rate in initiation of the HPV vaccine (primary outcome) and vaccine completion (secondary outcome) compared to historical baseline vaccination rate (control) among PLWH. It is hypothesized after implementation of the 4 Pillars™ program, we estimate an uptake rate of > = 13.5% in initiation of HPV vaccination.Identify mediators and potential moderators (HPV knowledge and awareness and vaccine hesitancy) of the intervention effects on HPV vaccination.Assess the sustainability of the intervention in vaccine uptake post-intervention and assess scalability of the program for wider implementation via a future national randomized control trial.

**Table 2 Tab2:** Overview of selected intervention strategies guided by the 4 Pillars™ Program

Pillar Strategy	Level	Intervention Component
Pillar 1: Convenience	Provider-	• Incorporate recommendation of the HPV vaccine with each clinic visit. • Perform HPV vaccination on-site
Pillar 2: Communication and education	Patient-	• Provide patient education on risk of HPV-related cancer and benefit of HPV vaccination
Pillar 3: Enhanced systems	Clinic-	• Provider and staff education on HPV vaccination via an in-service training • Document vaccination in EMR system
Pillar 4: Motivation	Clinic- Provider- Patient-	• Clinic designated Immunization Champion to provide coaching and motivation of regularly tracked vaccination progress • Provide patient check-in, reminders, and motivation for HPV vaccine completion • Communicate vaccination reminders by text, phone, and social media messaging

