## Methods/design

A pre-post intervention study design is used where HPV vaccination initiation and completion rates are measured before and after the intervention across the same clinics and enrolled participants (Fig. 1). HPV vaccination uptake 18 months before intervention will be queried from electronic medical records (EMR) and Georgia Registry of Immunization Transactions and Services (GRITS), which will serve as the historical control. GRITS is a population-based web application containing consolidated demographic and immunization history information. The use of a concurrent control is to reassess the background HPV uptake rate among PLWH during an adjacent time-period to post-intervention and similar population resources. The comparison of HPV vaccination rates pre- and post-intervention in the three selected representative HIV clinics in Georgia will be an exploratory goal of the trial due to the retrospective approach in the control phase and the prospective approach in the post intervention phase. A “within” analysis will be conducted to compare sites both pre- and post-intervention.

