### Patient-level intervention approach

Eligible and consenting participants (*n* = 365) will be part of the intervention group and will receive recommendation for the HPV vaccine from providers and clinic staff. Enrolled participants will also complete a self-administered questionnaire at enrollment on a HIPPA compliant online data management database on a tablet device. The survey questions will include sociodemographic characteristics, knowledge of and attitudes towards HPV, HPV vaccination, and anal cancer, and vaccine hesitancy. Participants will be requested to provide consent for their HPV vaccination history to be verified with electronic EMR and GRITS. Participants will then watch a short video on HPV and HPV vaccination that can be viewed on their phones (or the study’s tablet device) while waiting to be seen. Potential participants will be asked to follow the study’s private Facebook page which offers additional educational information tailored towards individuals with HIV on HPV-related disease and general health promotion, and risk reduction tips. The Facebook page will also utilize Facebook Messenger (commonly known as Messenger). The proposed study will utilize Messenger to send reminders for follow up appointments for the next shot in the series and motivational messaging to encourage and promote receipt of the HPV vaccine. Participants will be contacted to complete a post-evaluation survey administered via online, telephone, or a mailed paper copy at 6–9 months after baseline. Participants will receive $25 incentive for completion of baseline and follow up study activities.

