#### Data analyses of primary outcomes

For analysis of the primary (HPV vaccination initiation) and secondary endpoints (HPV vaccination completion), the uptake rate of HPV vaccination pre- and post-intervention will be estimated separately with a 95% exact confidence interval using all eligible cases from both phases. The one-sample binomial exact test will be used to test whether the rate after the intervention is higher than the baseline rate (P0 = 13.5%). We will also perform the Chi-square test to compare the rate change between control and interventional phases, which will be exploratory. Logistic regression will be used to further adjust background difference in study population in pre- and post- intervention phases. For the longitudinal data collected from the intervention phase, the data structure holds multi-level information from patients, providers, and clinic levels. The goal of the analyses is to identify the factors that might impact HPV uptake from each level of information, which might lead to the future improvement of implementation strategy. Data will be described using summary statistics (e.g., quartiles, median, mean, standard deviation) for continuous variables and marginal distribution (frequency and percentage) for categorical variables. The univariate association with the HPV vaccination (yes vs. no) will be tested in logistic regression for each variable separately. The change of survey response between baseline and a follow-up time point will be tested by paired tests (e.g., paired t-test, McNemar test). Along with data visualization, all above mentioned descriptive and univariate association analyses will be repeated within each of the three clinics. Data will be pooled to build the multilevel analysis models, we mainly consider using the mixed-effect model and/or Bayesian multilevel modeling, in which the random effect will be considered at provider and clinical levels. We will follow the key modeling considerations listed by J.J. Hox [29] to identify the significant mediators and moderators at different levels that impact the uptake of HPV vaccination.

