#### Statistical power

Based on our preliminary data, we found that HPV vaccination rate is around 13.5% (P0) in general, and another larger study in the literature found a very similar rate of 13.6% [10]. We powered the study to detect an uptake rate > 13.5% after the intervention. Thus, a sample size of 317 achieves 80% power to detect a superiority difference of 5% (PB-P0) using an exact one-sided test with a significance level (alpha) of 0.05. We anticipate a 5% superiority difference is reasonable to achieve with an uptake rate of 18.5% (PB) after the intervention. We will be able to reject the Null hypothesis and claim the uptake rate of > 13.5% after 54 patients have initiated the HPV test. After taking about 15% of the drop-off rate into account, we plan to include 365 participants among 3 clinics for the intervention phase. The calculation was by PASS 2020 for testing superiority of one proportion using the Exact test. The Null hypothesis is *P* < = 13.5% and the alternative hypothesis is *P* > 13.5%. For the control phase, we will query all eligible subjects from EMR database among the 3 clinics at 18 months pre-intervention, which could be approximately 2300 subjects [30]. Assuming we end up with the same number of subjects in both control (*N* = 317) and intervention phase (*N* = 317), we will have 81% statistical power to detect an HPV uptake rate difference of 9% (22.5% vs. 13.5%) by two-sided Fishers’ Exact Test and under significance level of 0.05. We anticipate such a difference would be feasible based on our best knowledge and the literature. Regarding the patient- level component of the intervention, all incoming eligible patients will be influenced, and hence 365 participants are the minimum number to capture the follow-up information, the actual number of sample size used for the calculation of HPV vaccination rate will be larger as the vaccination status will be captured automatically in EMR without a consent.

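### Mediation and moderation of the intervention effect by HPV knowledge and vaccine hesitancy (Aim 3) cannot be estimated, because only intervened participants are surveyed

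*Protocol article*

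**What the plan says.** The third specific aim in the Background is to "Identify mediators and potential moderators (HPV knowledge and awareness and vaccine hesitancy) of the intervention effects on HPV vaccination". The abstract's Methods paragraph widens the list and gives every variable both roles: "Sociodemographic, HPV knowledge, and vaccine hesitancy will be assessed as mediators and moderators for HPV vaccination". The section on data analyses of primary outcomes says that multilevel models will be used "to identify the significant mediators and moderators at different levels that impact the uptake of HPV vaccination". The same section places that work in the intervention-phase data and describes its goal as finding factors that may affect uptake.

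On data sources:

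- **Survey.** The section on the patient-level intervention approach says "Enrolled participants will also complete a self-administered questionnaire at enrollment". The questionnaire covers sociodemographics, knowledge and attitudes, and vaccine hesitancy. The same section places all consenting participants (n = 365) in the intervention group.
- **Follow-up survey.** "Participants will be contacted to complete a post-evaluation survey administered via online, telephone, or a mailed paper copy", timed at 6–9 months after baseline.
- **Control.** Under Statistical power: "For the control phase, we will query all eligible subjects from EMR database among the 3 clinics at 18 months pre-intervention", approximately 2300 people. Methods/design likewise describes a retrospective query of electronic medical records (EMR) and the state immunization registry (GRITS). Neither section mentions a patient survey.
- **Vaccination.** The clinic-level section asks staff to recommend and give the vaccine at every routine visit. Initiation is assessed at 24 months.

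**The concern.** A mediator of an intervention effect is something the intervention changes and through which it changes the outcome. A moderator is something over whose levels the effect differs. Both need a contrast between intervened and non-intervened people in whom the variable is known. Here the two variables named in Aim 3 are known only on the intervened side.

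A mediator must also be measured before the outcome. The only post-intervention measurement is at 6–9 months, while the vaccine can be given from the first visit onward.

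At stake is what the trial may conclude about mechanism. If patients with better knowledge or less hesitancy are vaccinated more often, that is a correlate of uptake within one exposed group. Reported as a mediator or moderator, it would be read as evidence of how, or for whom, the programme works. The analysis section says these results may inform later implementation, and Aim 4 looks ahead to a national randomised trial.

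**Working it through.** The plan states no figure on this point, so the check concerns what can be estimated and in what time order.

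**1. What is observed.** Let T = 0 for the historical control and T = 1 for the intervention phase. Let M be a knowledge or hesitancy score and Y be initiation.

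| | T = 0 | T = 1, enrolled | T = 1, not enrolled |
|---|---|---|---|
| Y (EMR/GRITS) | yes | yes | yes |
| Age, gender, race, insurance, clinic | yes | yes | yes |
| M (survey) | no | yes | no |

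The third column arises because Statistical power says that vaccination status will be captured for more patients than the 365, without consent. These patients have no survey, and the same section counts all incoming eligible patients as influenced by the programme, so they are not an unexposed group either.

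**2. Moderation by M.** The quantity needed is how [E(Y | T=1, M=m) − E(Y | T=0, M=m)] varies with m. The second term has no data.

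**3. Mediation by M.** The first leg is E(M | T=1) − E(M | T=0). Again the second term has no data. The second leg, the association of M with Y given T, can be fitted only at T = 1.

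**4. Rank.** Take the model with columns 1, T, M and T×M. Every row with M observed has T = 1, so column T equals column 1 and column T×M equals column M. The rank is 2 of 4. What remains is an intercept and a slope of Y on M among intervened participants.

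**5. Variables seen in both phases.** The Process evaluation section adjusts the pre-post change for age, gender, race and insurance, and the same three clinics supply both phases. For these, the phase-by-variable term can be fitted.

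**6. Time order.** Enrolment takes place while patients wait to be seen, so a first dose is possible that day. No stated rule puts the follow-up survey before the first dose. The documents do not give the timing of initiation, so the following is an illustration under assumptions. Take 18.5% initiating over 24 months (the design rate) at constant hazard:

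- λ = −ln(1 − 0.185)/24 = 0.2046/24 = 0.00852 per month
- share of initiations before month m = (1 − e^(−λm))/0.185
- m = 6: 0.0499/0.185 = 27%
- m = 9: 0.0738/0.185 = 40%

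If a share d of initiations occurs at the enrolment visit and the rest follows this pattern, the share before the survey is d + (1 − d) × the value above:

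| assumed d | survey at 6 months | survey at 9 months |
|---|---|---|
| 0 | 27% | 40% |
| 0.3 | 49% | 58% |
| 0.6 | 71% | 76% |

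With the plan's 317 after drop-off, initiators number 317 × 0.185 = 58.6. At d = 0, about 16 (27%) to 23 (40%) of them would have their follow-up score measured after the event.

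**The case against.** - **The analysis section already aims at factors affecting uptake, within intervention-phase data, and tests survey change by paired tests.** This is true, and it means much of the remedy is already in the plan. It does not settle the matter: the same section, Aim 3 and the abstract all still promise mediators and moderators.
- **Exposure is not constant if intensity varies.** Training is optional for staff, following the social media page is optional for patients, and the process evaluation records the extent of delivery. Intensity may well vary. However, the plan does not name it as the exposure, and the variation is self-selected.
- **Enrolled participants are their own control.** Methods/design does speak of rates before and after in the same participants, and the enrolment survey precedes the video. The within-person change in score can therefore be described. But eligibility selects on earlier vaccination status, so these people's pre-period outcome is truncated, and the survey is taken only at the end of that period. Change over 6–9 months also mixes the programme with time, repeat questioning and vaccination itself.
- **Demographic moderation remains possible.** This stands. A reader might infer that no moderation at all can be estimated; that goes too far, because demographics and clinic are available in both phases.
- **The time-order problem may be small.** A reader might infer that the mediator is usually measured after the outcome. The documents give no such figure. Under constant hazard most initiations would follow the survey, and the higher shares rest on assumed same-day vaccination. The problem also does not touch enrolment scores.
- **A clinic random effect with only three clinics.** A reader might count this as a further error. The plan says only "in which the random effect will be considered at provider and clinical levels" and allows Bayesian models, so a fixed clinic effect would be a modelling preference and is not part of this point.

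**Conclusion.** The concern holds for HPV knowledge/awareness and vaccine hesitancy, measured against the historical control. For these two variables neither mediation nor moderation of the intervention effect can be estimated; only their association with uptake among intervened participants can. This follows from who is surveyed and does not depend on any numerical assumption. An analysis plan cannot repair it, since a retrospective records query cannot recover past survey scores.

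The second part is narrower: a follow-up score used as a mediator can post-date the first dose. How often this happens is unknown, and the 27% to 40% rests on the assumed constant hazard and the 18.5% design rate.

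The primary and secondary endpoint tests are unaffected. The point should be corrected, because a named aim cannot be met as written.

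**What to change.** 1. Restate Aim 3, and the matching sentences in the abstract and the section on data analyses of primary outcomes, as patient-, provider- and clinic-level predictors of initiation among intervention participants. Remove mediators and moderators as labels for knowledge and hesitancy.
2. Use the enrolment survey scores as the predictors.
3. Report the baseline-to-follow-up change in score as a separate pre-post outcome. Link it to initiation only where the follow-up survey precedes the first dose: take participants still unvaccinated at their survey date and count initiation after it.
4. Limit moderation of the pre-post effect to variables available in both phases (age, gender, race, insurance, clinic). Test it by phase-by-variable interactions and label it exploratory, in keeping with the status that Methods/design gives the pre-post comparison.

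**Cost.** Rewording and a tighter model statement; no new data. Aim 3 makes a more modest claim. Step 3 also loses events: in the constant-hazard illustration, 58.6 − 23.4 = 35 to 58.6 − 15.8 = 43 initiators would remain, so that analysis would be imprecise. If the mechanism claim is to be kept, the survey would have to be given to a comparison group that has not received the intervention, which is a different study.
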